|                                                 | Pulse oximetry                                       | X*                     | X                  | X*                                               | X                                   | X*                        | X*                          | X              |                     |                                             |
|                                                 | Type of mechanical ventilation                       |                        | X                  | X                                                | X                                   | X                         | X                           | X              |                     |                                             |
|                                                 | Urine output                                         | X                      | X                  | X                                                | X                                   | X                         | X                           | X              |                     |                                             |
| primary outcome                                 |                                                      |                        |                    |                                                  | X                                   |                           |                             | X              |                     |                                             |
| Secondary outcomes                              |                                                      |                        |                    |                                                  |                                     |                           |                             |                | D                   |                                             |

X : Indicates Mandatory Procedures that should be entered into the eCRF;

X\*: Indicates data entered into the eCRF if available;

Pd\*: Indicates non-mandatory pharmacodynamics assessment at the visit that should be entered into the eCRF if available

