A significant proportion of babies born at less than 32 weeks' gestation require cardiovascular treatment in the hours after birth, even in the absence of identifiable pathologies. This indicates that haemodynamic insufficiency in this age group can be related to an immature adaptation to birth.

The conventional approach to infants at risk of haemodynamic insufficiency is to monitor the babies using clinical signs, mostly blood pressure. However, blood pressure is a poor surrogate of systemic and organ (including brain) blood flow during the transitional period from intra- to extra- uterine life. This state is characterised by increased peripheral vascular resistance and therefore increased afterload, which may cause myocardial dysfunction and impaired blood flow in spite of 'normal' central blood pressure.

We propose an alternative approach, which focuses on evidence of blood flow distribution and poor perfusion. One pilot, randomised placebo-controlled trial on dobutamine for early haemodynamic insufficiency, defined as low SVC flow ( $<41$  ml/kg/min), conducted in infants below 31 completed weeks' gestation, has been recently published (11). Eligible infants were prospectively evaluated for several parameters of circulatory impairment from birth, and randomised to dobutamine or placebo in case of low SVC flow within the first 24 hours. An analysis in retrospect of the non-randomised infants, looking at biomarkers that would qualify as a criterion for inclusion of patients in a future phase III clinical trial to demonstrate efficacy for cardiovascular treatment in the indication under investigation, found SVC flow  $<51$  ml/kg/min, mean arterial blood pressure (MABP)  $<$  gestational age (GA)-5 mmHg, and lactate above 4 mmol/L as the biomarkers that better predicted combined adverse outcome (death or severe intracranial haemorrhage or white matter damage)(12). The use of a combination of biomarkers that have been proven to be as good predictors for adverse outcome, will better define the population at risk of end-organ damage due to abnormal blood flow distribution that eventually would benefit of cardiovascular treatment.

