## 5 STUDY POPULATION

### 5.1 INCLUSION CRITERIA

Infants are eligible to be included in the study only if they meet **all** the following criteria:

- Born up to 32(+6) weeks gestation
- Presence of haemodynamic insufficiency, defined as SVC flow <51 ml/kg/min.
- Provision of signed and dated informed consent form by father/mother or legally designated representative, which can be given antenatally as described in section 5.4.

Three notes of caution are necessary with respect to inclusion of infants into this trial:

- The treating physician needs to be at “clinical” equipoise on providing the proposed trial of dobutamine-treatment to the infant, which can be justified as explained in section 2.1 above.
- To avoid over treatment, the treating physician needs to fully understand the determinant of the pathophysiology of circulatory impairment and use clinical judgment to decide treatment. For example, during severe congenital anaemia a baby meeting the inclusion criteria will not be included and will instead get the required blood volume replacement first; and only afterwards could be considered for inclusion if still eligible.
- Deferred informed consent and prior informed assent (opt-out with enrollment as default) are plausible in this condition because it is in accord with Article 35 of the Regulation of the European Union on Clinical Trials (Regulations (EU) no536/2014), that states: Informed consent to participate in a clinical trial may be obtained, and information on the clinical trial may be given, after the decision to include the subject in the trial, provided that this decision is taken at the time of the first intervention on the subject, in accordance with the protocol for that clinical trial and that all the following conditions are fulfilled:
  - Urgency of the situation, caused by a sudden life-threatening or other serious medical condition
  - Scientific grounds to expect that participation of the subject in the trial will have the potential to produce a direct clinically relevant benefit for the subject resulting in a measurable health-related improvement or in the diagnosis of its condition

- It is not possible within the therapeutic window to supply all prior information to and obtain prior informed consent from his/her legally designated representative
- The investigator certifies that he or she is not aware of any objections to participate in the clinical trial previously expressed by the legally designated representative

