#### *8.1.1.4 Treatment: PD/PK Assessment Visit*

The patient PD response to the dobutamine treatment should be evaluated at 60 minutes from the start of effective dose infusion, to establish if the treatment success dose has been achieved. Blood sample (1 millilitre) will be taken.

Effective dose infusion is define as the time ( $t_0$ ) when the study medication enters blood stream, which is calculated according to the following equation:

$$t_0 = t_{\text{switch on}} + t_d$$

$$t_d (\text{min}) = (\text{volume (ml)} / \text{velocity (ml/h)}) \times 60 (\text{min/h}),$$

where *volume* refers to the catheter lumen plus the stopcock dead space and *velocity* refers to the summation of the infusion rate of all the infusions coming through the line. Dobutamine infusion should be at the stopcock closest to the catheter entry. Before dobutamine is connected to the stopcock, the whole system (including bionector) will be fed with the dobutamine solution and the pump will be switched on for a few minutes to ensure that no pulling out effect is added at start. The pump will be switched off and the system will be connected to the stopcock. Finally the pump will be switched on and the time will be registered ( $t_{\text{switch on}}$ )

The following criteria will be checked at every patient at the dose evaluation:

- Main response biomarker: SVC flow > 55 ml/kg/min

And other parameters:

- MABP increase by 20% (roughly 4-6 mmHg)
- Decreasing serum lactate levels
- Base excess levels being less negative
- CRT < 4 sec

Throughout the treatment, a series of clinical and biochemical parameters described in sections 8.1.2 below are evaluated and recorded in the eCRF according to the timings given in the section 1.3.

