#### 8.1.1.6 Efficacy Visit

To test whether dobutamine alone achieved and maintained an acceptable haemodynamic status during the first 72 h from birth (secondary objective).

This study short-term efficacy outcome means that at 72h the infant is alive, and the clinical condition is:

- SVC flow > 55 ml/kg/min;
- MABP > GA;
- Decreasing serum lactate levels;
- CRT < 4s;
- Urine output > 1 ml/kg/h;
- Dobutamine alone was used (regardless the dose).

Investigators will be asked to report if, according to this definition, short-term success has been achieved or not. If not, investigators will also be asked to check if persistent circulatory failure or death is due to something different from pure transitional circulation adaptation, e.g., sepsis, haemodynamically significant PDA, air trapping (lung over distension), pneumothorax, pleural or pericardiac effusion.

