### 8.1.2.3 Clinical and Biochemical Parameters

The clinical and biochemical parameters listed next will be recorded and entered into the eCRF at the study time points indicated in section 1.3 (SoA):

- Physical and vital signs: heart rate; blood pressure (systolic, mean and diastolic); pulse oximetry ( $\text{SpO}_2$ ); capillary refill time (CRT); and type of mechanical ventilation (CPAP, MV, HFOV, HFNC; none).
- Biochemical parameters (from clinically indicated blood samples): pH;  $\text{pCO}_2$ ; lactate; base excess; haemoglobin; creatinine; C-reactive protein; glucose. The volume of blood required for these samples is 0.3 ml to 0.5 ml, approximately.
- Urine output every 4 hours.
- SVC flow and RVO as clinical parameters: echocardiography (Echo-D) will be performed as soon as possible after birth, during screening phase, and during treatment phase for PD assessment of the study medication. At each Echo-D scan, SVC flow and RVO will be measured and recorded in the eCRF as indicated in SoA table (section 1.3). SVC flow will be measured using the traditional technique of Kluckow & Evans (29) which assesses SVC diameter from a parasternal long-axis view and flow velocity from low subcostal view by averaging 5-10 cardiac cycles (43).

- Routine evaluation for PDA is not mandated per protocol at each Echo-D; however, PDA assessment will be done when clinically indicated.

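### The 72-h success list requires a falling lactate, although entry needs no raised lactate and lactate is the only measured item on that list that is optional at 72 h

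*Protocol*

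**What the plan says.** Section 8.1.1.6 (Efficacy Visit) says that it tests the secondary objective on haemodynamic status over the first 72 h, and gives its own definition: "This study short-term efficacy outcome means that at 72h the infant is alive, and the clinical condition is", followed by six items. These are SVC flow above 55 ml/kg/min, MABP above GA, "Decreasing serum lactate levels", CRT below 4 s, urine output above 1 ml/kg/h, and use of dobutamine alone. Scoring is then binary: "Investigators will be asked to report if, according to this definition, short-term success has been achieved or not".

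The haemodynamic entry condition in section 5.1 is "Presence of haemodynamic insufficiency, defined as SVC flow <51 ml/kg/min". No inclusion criterion mentions lactate.

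In the Schedule of Assessments (section 1.2) the lactate row carries X* at all seven visits from screening to 72 h. The legend explains X* as "Indicates data entered into the eCRF if available". Section 8.1.2.3 gives the source of the values: "Biochemical parameters (from clinically indicated blood samples".

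A lactate level appears in the background, section 2.1.1, where a retrospective analysis found "lactate above 4 mmol/L as the biomarkers that better predicted combined adverse outcome". That level is not carried into the entry criteria or the 72-h list.

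Footnote [B] (synopsis and section 3) defines the same secondary endpoint differently. There, acceptable status means reaching and keeping dose success through 72 h, and it is lost when cardiovascular treatment beyond dobutamine alone is brought in, or on death. Footnote [B] contains no lactate item.

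**The concern.** Four of the five measured items are levels that can be read off at 72 h. Lactate alone is a change, so it needs a starting point and two values. The protocol names no starting point and guarantees neither value.

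This causes two problems. First, an infant can enter on low SVC flow with a normal lactate, which then has nothing to fall from. If it stays normal, the infant fails the item while meeting everything else. Second, an infant whose attending team saw no reason to draw blood has no direction to report.

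At stake is the secondary efficacy proportion. Wherever this list is used, an infant who recovered on dobutamine alone may be counted as a failure or left unscored for reasons unrelated to response. Common sense at the bedside would soften this, but in an unblinded trial with at most 30 infants it would mean that scoring depends on the assessor.

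**Working it through.** No sample size, power or error rate depends on this item, so there is no stated figure to reproduce. The check sets the 72-h list against the Schedule and then gives the weight of one infant.

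**The list against the Schedule, 72-h column**

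| Item in 8.1.1.6 | Form | Code at 72 h |
|---|---|---|
| SVC flow | level | X (mandatory) |
| MABP | level | X (mandatory, BP row) |
| Lactate | direction | X* (if available) |
| CRT | level | X (mandatory) |
| Urine output | level | X (mandatory) |
| Dobutamine alone | treatment record | not a measurement |

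Lactate is the only measured item that is optional at 72 h. Base excess, which is not on the list, is mandatory there.

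**Literal scoring of an infant who meets every other item**

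1. Lactate raised at the reference sample and lower later: success.
2. Lactate normal at the reference sample and unchanged: not decreasing, so failure.
3. Fewer than two lactate values: no direction exists, so the item cannot be scored.

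The entry criterion permits case 2. The X* coding, together with sampling only on clinical indication, permits case 3.

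**Weight of one infant.** The maximum sample size is 30 (section 9.1.1). One reclassified infant moves the proportion by 1/30 = 3.3 percentage points.

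**Illustration only.** The documents give no lactate distribution and no sampling rate, so every share below is an assumption. Let R infants out of 30 meet every other item, and let a share s of them have a normal, stable lactate. Scored success is R × (1 − s) / 30.

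| Share s | R = 24 (80%) | R = 18 (60%) |
|---|---|---|
| 10% | 21.6/30 = 72% | 16.2/30 = 54% |
| 20% | 19.2/30 = 64% | 14.4/30 = 48% |
| 30% | 16.8/30 = 56% | 12.6/30 = 42% |
| 50% | 12/30 = 40% | 9/30 = 30% |

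Suppose instead that two samples are compared mechanically and noise makes the second one lower half the time. With R = 24 and s between 25% and 75%, the loss is then 24 × 0.25 × 0.5 = 3 to 24 × 0.75 × 0.5 = 9 infants, giving 21/30 = 70% to 15/30 = 50%. The two models differ widely, which shows how far the size depends on unstated inputs.

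For missing values, if m infants meet every other item but lack two lactates, best-case and worst-case scoring differ by m/30. For m = 3, 6, 9 and 12 that is 10, 20, 30 and 40 percentage points.

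**The case against.** The strongest counter-argument is that this list may not govern the analysis. Footnote [B] is the formal endpoint text and has no lactate item, and section 9.1.2 speaks of loss of acceptable status, which is footnote [B]'s language. An analysis under [B] would avoid the problem. This stands in part. However, section 8.1.1.6 says that its own list tests this secondary objective and has investigators score by it, so the conflict has to be resolved and cannot be used to set the flaw aside.

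A second argument is that reference samples, windows and missing components are commonly left to the SAP, which is not shown. That is fair for the missing-data rule alone. But the protocol itself fixes the wording, the yes/no report and the optional sampling, and an SAP cannot recover a lactate that was never drawn.

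Third, the six items are not introduced as all being required. The sentence that introduces them is still most naturally read that way.

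A reader might also infer that the 60-minute evaluation in section 8.1.1.4 has the same fault, because "The following criteria will be checked at every patient at the dose evaluation" covers lactate, base excess and CRT. The documents do not support this as an equal problem. That section separates SVC flow as the main biomarker from the other parameters and refers to the Schedule for timings, and the primary endpoint uses SVC flow alone. CRT is coded Pd at that visit, a code the legend does not define, so it is not shown to be optional.

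**Conclusion.** The point holds as a defect in the wording of a secondary endpoint. It rests on two readings: that all six items are required, and that decreasing is taken literally. On those readings the rule fails a recovered infant with a normal, stable lactate and cannot score one without two values. Each such infant is worth 3.3 percentage points at N = 30.

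A reader might go further and infer a bias of a given size, for example a fall from 80% to between 50% and 70%. The documents do not support any such figure; it comes wholly from assumed shares. It is plausible that lactate is missing more often in infants who look well, since samples are drawn on clinical indication, but the protocol has no data on this.

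The primary endpoint, the allocation of doses and the planned 30 infants are unaffected, and section 9.1.2 attaches no test or threshold to this proportion. The change should be made because it is cheap, but the trial's main result does not depend on it.

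**What to change.** In section 8.1.1.6:

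- Reword the lactate item so that it is also met by a lactate that was normal at the reference sample and is still normal. The sponsor should prespecify the normal limit. The 4 mmol/L in section 2.1.1 is a retrospective marker of risk, so it is only one candidate.
- Name the reference sample, for example Baseline, and a window before 72 h for the later sample. With Baseline as reference, an infant whose raised lactate normalised early and then stayed flat also passes.
- Prespecify one scoring rule for missing lactate. Add a sensitivity analysis that scores success without the lactate item for all infants, so that sampling practice cannot drive the result. Dropping the item only for unsampled infants would give sampled infants an extra hurdle.
- Reconcile the list with footnote [B] and state which one defines the analysed endpoint.

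A simple cut at 4 mmol/L, with any fall accepted above it, would not be enough. It would pass a rise from 1.0 to 3.9 and a fall from 10.0 to 9.9.

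The cost is a short rewording, a matching note in the Schedule and eCRF, and no additional blood draw. The downside is a slightly less strict item and one extra sensitivity analysis.

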#### 8.1.1.7 End of Treatment Assessment:

Weaning and stopping of the dobutamine infusion will be at the criteria of attending physician, proceeding as done in clinical practice for other catecholamine treatment and following local policies. Therefore, no set guidance is provided per protocol, although it is recommended to follow the same down-titration scheme as up-titration.

The End of Treatment Assessment Visit occurs at treatment completion, when the dobutamine infusion has been stopped.

#### 8.1.1.8 Mid and Long-term assessment.

Visit at 36±2 weeks PMA to record main neonatal clinical outcomes, included bronchopulmonary dysplasia, necrotizing enterocolitis, retinopathy of prematurity and neurological complications (cerebral haemorrhage grade II or III, periventricular haemorrhagic infarction, white matter injury, post-haemorrhagic ventricular dilatation, cerebellar haemorrhage or cerebral atrophy).

Long-term follow up of the study population will take place at 24 (±4) months of age corrected for prematurity. However, it is not feasible to precise which will be the first patient assessed because will depend on prematurity. We provide 28-months period to complete the long-term follow up of the whole study population. Within this timeframe, there is margin for a complete follow up even for the latest patients enrolled irrespective of their immaturity (how low the gestational age was at birth). The follow up will include growth assessment (weight, height and head circumference), general health, structured neurological examination and neurodevelopmental testing.

### 8.1.2 Basic Evaluations

The procedures and evaluations described in this section will be undertaken according to the timing described in the SoA table (Section 1.3).

### 8.1.2.1 Medical History

The following data will be captured from the participant's clinical records:

- Demographic data: date of birth and gender
- Maternal data: Antenatal corticosteroid use (complete course); Maternal hypertension and treatment; Chorioamnionitis: fever ( $>38^{\circ}\text{C}$ ), foul smelling amniotic fluid, tenderness of the uterus, maternal/foetal tachycardia, maternal leukocytosis, histo-pathological diagnosis; Prolonged rupture of membranes ( $>24$  hours to delivery); Type of delivery; Any other relevant condition.
- Perinatal data: Gestational age; Multiple (order); Need for advanced resuscitation at birth (intubation $\pm$  assisted ventilation); Placental transfusion procedure (delayed cord clamping, milking of the cord); Birth weight; 5 min Apgar score; SNAPPE-II score (42); Surfactant.
- Neonatal outcomes: overall mortality; cUS diagnoses; Necrotising enterocolitis or bowel perforation; bronchopulmonary dysplasia (oxygen dependency at 36 week' gestation); early infection (positive cultures or CRP  $<72\text{h}$  of birth); nosocomial infection (use of antibiotics for at least 5 days regardless of negative or positive blood culture); patent ductus arteriosus (PDA) and treatment; retinopathy of prematurity (ROP) and treatment, discharge date, discharge type (home, transfer to other hospital).

### 8.1.2.2 Medication

The maximum dobutamine dose infusion in the first 72h from birth will be recorded in the eCRF.

All co-existent diseases or conditions will be treated in accordance with prevailing medical practice. All allowed medications that have been started before screening may be continued during the study (see also section 6.3).

The need for additional cardiovascular support to that specified for the clinical trial will also be recorded.

### 8.1.2.3 Clinical and Biochemical Parameters

The clinical and biochemical parameters listed next will be recorded and entered into the eCRF at the study time points indicated in section 1.3 (SoA):

- Physical and vital signs: heart rate; blood pressure (systolic, mean and diastolic); pulse oximetry ( $\text{SpO}_2$ ); capillary refill time (CRT); and type of mechanical ventilation (CPAP, MV, HFOV, HFNC; none).
- Biochemical parameters (from clinically indicated blood samples): pH;  $\text{pCO}_2$ ; lactate; base excess; haemoglobin; creatinine; C-reactive protein; glucose. The volume of blood required for these samples is 0.3 ml to 0.5 ml, approximately.
- Urine output every 4 hours.
- SVC flow and RVO as clinical parameters: echocardiography (Echo-D) will be performed as soon as possible after birth, during screening phase, and during treatment phase for PD assessment of the study medication. At each Echo-D scan, SVC flow and RVO will be measured and recorded in the eCRF as indicated in SoA table (section 1.3). SVC flow will be measured using the traditional technique of Kluckow & Evans (29) which assesses SVC diameter from a parasternal long-axis view and flow velocity from low subcostal view by averaging 5-10 cardiac cycles (43).

- Routine evaluation for PDA is not mandated per protocol at each Echo-D; however, PDA assessment will be done when clinically indicated.

